### Masking

It is not possible to conceal study arm allocation from patients, clinicians or investigators. However data extractors will be masked, except when extracting audio and video related information which will be collected for the intervention arm only.

### Patient recruitment

Patients will be recruited from the referring hospital paediatric wards, emergency departments or adult intensive care units.

Initial contact between the referring hospital clinician and RSQ will always be made by telephone (Figure 1). On receiving that call, the RSQ nurse co-ordinators, will then also contact the designated PICU consultant by telephone. Using the randomisation process, the PICU consultant will determine whether the consultation continues by telephone (usual care, control arm), or by telemedicine (intervention arm). While all parties will aim to comply with the study protocol, there may be circumstances under which the referring and PICU clinicians elect to override the randomisation process in the interest of the care of the child. The resulting loss of study cases will be monitored and recorded on a daily basis.

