### Randomisation

Generation of intervention/control arm allocation sequences will occur centrally. Sequences will be generated using permuted block randomisation, with random block sizes of 6,8 or 10 entries and a 1:1 allocation ratio using an online true random number generation service [19]. The process of generating these sequences will be conducted by an independent party. Four tables of random numbers will be generated, one for each study site. Odd numbers will denote allocation to the control arm and even numbers to the intervention. The tables will be held securely on a server on a private network.

A password-protected custom application (accessible by computer or portable device), driven by the random number tables, will be provided for the PICU clinicians to determine cases and controls at time of initial retrieval call from RSQ. The application will record all accesses and allocations.

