### Sample size

In this study, resources limit the number of study sites to four and the study duration to 24 months. It is estimated that during the study period there will be 200 retrieval calls relating to eligible participants. We estimate an 80% participation rate (20% attrition due to lack of consent or clinicians electing not to consult by telemedicine and continuing by telephone) and consequently estimate the study will recruit a total of 160 retrieval participants with 80 in each arm. Retrospective stabilisation time data for the study sites showed a standard deviation of 41 minutes. With alpha = 0.05 we have 80% power to detect a clinically important difference in stabilisation time between-consultation types of 18 minutes or greater.

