### Data analysis

Data analysis will be conducted under the intention-to-treat (ITT) principle. Descriptive data will be presented as either mean (standard deviation) or median (25th to 75th percentile) for continuous data depending on its distribution, and as frequency (percentage) for categorical data. Statistical analyses for each outcome variable are shown in Table 2. All statistical analyses will be conducted using Stata (Statacorp, College Station).

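### Children whose allocation is overridden are counted as lost in the recruitment and sample-size text although the analysis is stated as intention-to-treat; excluding them would put the primary comparison at risk of bias, and keeping them lowers the stated power

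*Protocol article*

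**What the plan says.** All references are to the protocol article.

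- **Randomisation.** PICU clinicians use an application "to determine cases and controls at time of initial retrieval call from RSQ". The section adds: "The application will record all accesses and allocations".
- **Masking.** "It is not possible to conceal study arm allocation from patients, clinicians or investigators".
- **Patient recruitment.** The PICU consultant uses the randomisation process to set the mode of consultation. The text then says that the referring and PICU clinicians may "elect to override the randomisation process in the interest of the care of the child", and continues: "The resulting loss of study cases will be monitored and recorded on a daily basis".
- **Sample size.** The estimate is that "there will be 200 retrieval calls relating to eligible participants". An 80% participation rate is assumed and explained as "20% attrition due to lack of consent or clinicians electing not to consult by telemedicine and continuing by telephone". This leaves 160 participants, 80 per arm.
- **Data analysis.** "Data analysis will be conducted under the intention-to-treat (ITT) principle".

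No section says that a child whose allocation was overridden is followed and analysed in the allocated arm.

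**The concern.** Under intention-to-treat, a child allocated to telemedicine but consulted by telephone is non-adherent and not lost. The recruitment and sample-size sections treat that child as gone, while the analysis section requires the child to stay. A team that follows the first two sections literally would drop allocated children on clinical judgement, in a trial where the clinicians know the allocation.

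Telephone is the control, so a departure from telemedicine to telephone can occur only in the telemedicine arm. If overrides relate to how ill the child is, and illness relates to stabilisation time, excluding these children makes the arms differ for reasons other than the consultation. The affected quantity is the primary outcome.

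**Working it through.** **Order of events.** Patient recruitment puts the override after the step at which the consultant uses the randomisation, and Randomisation has the allocation opened at the initial call. The natural reading is that the child already has an allocation when it is overridden.

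**The plan's own figure.** Inputs from Sample size: SD 41 minutes, difference 18 minutes, alpha 0.05 (taken as two-sided), 80 per arm.
- 200 × 0.80 = 160.
- SE = 41 × √(2/80) = 6.48; 18/6.48 = 2.78; power = Φ(2.78 − 1.96) = 79.3%.

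The stated 80% is reproduced, so the sample-size arithmetic is not the error.

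**Assumptions for the rest.** The 200 calls are randomised 100:100 and 40 are lost. The document does not split the 40 between non-consent and override, so a range is shown. Non-consent falls equally on both arms, and overrides fall only on telemedicine. With k overrides, each arm has n = 100 − (40 − k)/2 consented children, and the overridden share of the telemedicine arm is f = k/n.

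**If overridden children are excluded.** Let D be the difference in mean stabilisation time between overridden and other children when telemedicine has no effect. D is assumed here; the document gives no value.
- Spurious difference b = f × D.
- SE = 41 × √(1/n + 1/(n − k)).
- Type I error = Φ(−1.96 + b/SE) + Φ(−1.96 − b/SE).

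Example with k = 20 and D = 20: n = 90, f = 20/90 = 0.222, b = 4.4, SE = 41 × √(1/90 + 1/70) = 6.53, b/SE = 0.68, and type I error = Φ(−1.28) + Φ(−2.64) = 10.4%.

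| Overrides | Telephone vs telemedicine | Telemedicine arm removed | Power for 18 min | b, D = 20 | Type I, D = 20 | Type I, D = 10 |
|---|---|---|---|---|---|---|
| 10 | 85 vs 75 | 12% | 79.1% | 2.4 min | 7% | 5% |
| 20 | 90 vs 70 | 22% | 78.7% | 4.4 min | 10% | 6% |
| 30 | 95 vs 65 | 32% | 77.9% | 6.3 min | 16% | 8% |
| 40 | 100 vs 60 | 40% | 76.7% | 8.0 min | 22% | 9% |

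Power hardly moves, so the risk is bias and not loss of precision. With D = 0 there is no bias. With D negative the sign of b reverses. The figures are before adjustment for PIM3. None of the four splits gives the stated 80 per arm.

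**If overridden children are kept (intention-to-treat).** Suppose they gain nothing from their allocation. The expected difference is then 18 × (1 − f), with SE = 41 × √(2/n). Example with k = 20: 18 × (1 − 0.222) = 14.0; SE = 41 × √(2/90) = 6.11; 14.0/6.11 = 2.29; power = Φ(0.33) = 63%.

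| Overrides | n per arm | Power, undiluted 18 min | Diluted difference | Power, diluted |
|---|---|---|---|---|
| 10 | 85 | 82% | 15.9 min | 71% |
| 20 | 90 | 84% | 14.0 min | 63% |
| 30 | 95 | 86% | 12.3 min | 54% |
| 40 | 100 | 87% | 10.8 min | 46% |

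**The case against.** The strongest reply is that the document never says an allocated child is dropped from the analysis. Intention-to-treat is stated without exception, every allocation is logged, and the disputed wording sits under recruitment and sample size. Overriding the randomisation process could mean bypassing it before the allocation is opened. Since first contact is always by telephone, continuing by telephone also fits a decision made before allocation. On that reading these children are never randomised, 80 per arm is consistent, and there is neither bias nor dilution. The recruitment flowchart, which might settle the order, is not available in the text reviewed.

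This reading is possible but less natural, because the override is described after the randomisation step. Even if it is what was meant, the wording permits the harmful reading and needs correcting.

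Three further objections stand as limits on the point:
- Patient recruitment names no arm, so a control child moved to telemedicine is not ruled out. One-sidedness rests on a single clause in Sample size, which gives no split from non-consent.
- The prognosis of overridden children is not described.
- The primary model adjusts for PIM3, which would remove the part of any imbalance that PIM3 captures.

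**Conclusion.** The conflict is real. Two sections treat overridden children as lost, and a third commits to an analysis that keeps them. Excluding them would put the primary comparison at risk of bias. The illustrative size is 2.4 to 8.0 minutes and a type I error of about 7% to 22%. This assumes 10 to 40 overrides, all in the telemedicine arm, a 20-minute prognostic difference and no PIM3 adjustment.

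A reader might infer more: that the comparison is biased in favour of telemedicine because the most urgent children leave that arm. The document does not support this. It says only that overrides serve the child's care, not that these children are sicker or would take longer to stabilise. Direction and size therefore cannot be derived, and there is no bias if overridden children do not differ.

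Keeping them removes this source of bias but not the second consequence. The 80% power makes no allowance for dilution. If overridden children gain nothing, power for an 18-minute effect is 71% to 46% for 10 to 40 overrides. If 18 minutes is meant as the effect of allocation, overrides included, power is 82% to 87%.

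**What to change.** 1. In Patient recruitment, replace the sentence on lost cases with wording such as: *Every consented child with an allocation in the application log is followed and analysed in the allocated arm, whatever consultation was used. Overrides are reported by arm as non-adherence.*
2. In Sample size, count as attrition only non-consent and children who were never allocated. If some decisions to stay on the telephone are meant to precede allocation, say so in both sections.
3. Restate the power with an assumed override rate, and say whether 18 minutes is the effect of allocation or of receiving telemedicine.
4. Optionally, add a complier-average analysis with allocation as the instrument, labelled supplementary.

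The cost is small. Allocations are already logged, and Data collection takes outcomes from the retrieval form and patient chart, so the same sources serve overridden children. The real downside is a less favourable power figure. Clinicians' freedom to override is unchanged; only the analysis of these children is at issue.

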**Figure 1 Fig1:**
[figure not shown]
**Recruitment flowchart.**

#### Intervention arm-telemedicine

Patients randomised to the intervention arm will receive a consultation by real-time audio-visual telemedicine. This form of consultation allows clinicians to see and hear each other at a distance. It also allows the specialist at the PICU to remotely view the patient, medical images and medical equipment (e.g. the patient monitor and/or ventilator). Visual information will be used by the specialist when providing clinical advice, observing interventions and in managing retrievals. This form of telemedicine allows the clinician at the patient end to work hands free.

Custom designed telemedicine systems and associated infrastructure [20] will be installed at each site. The efficacy of these systems has been extensively tested in the controlled environments of a neonatal intensive care unit [21,22] and a PICU [23,24]. In some circumstances, consultations may also be conducted using existing health department video conferencing systems.

#### Control arm-usual care

Patients randomised to the control arm will receive a telephone consultation. During the consultation, clinical information such as the patient’s condition, descriptions of medical images and output/settings on medical equipment will be conveyed verbally. No visual information will be shared between hospitals. Telephone consultations of this style are the current usual practice in all four participating centres.

#### Advice-only calls

Advice-only calls will not be randomised and clinicians may elect to use telephone, or to use telemedicine, or possibly a combination of both. These calls will not be co-ordinated by RSQ, rather the referring hospital clinician will contact a clinician at the RCH PICU directly. These patients will not be recruited to the RCT, but will be recruited to a separate observational study.

### Outcome measures

Time points (*t0*–*t5*) in the retrieval process are shown in Figure 2.

**Figure 2 Fig2:**
[figure not shown]
**Retrieval process time points.**

#### Primary outcome measure

Stabilisation time (*ST*). Clinical time spent by the retrieval team with at the bedside at the referring hospital (*ST* = *time*_*t*3_ − *time*_*t*2_). We will analyse all participants after stratifying for initial risk, as measured using the Paediatric Index of Mortality 3 (PIM3) [14].

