### Objectives and hypotheses

#### Hypotheses

Consultation using real-time video-based telemedicine between a PICU consultant and a referring hospital clinician will:Clinical effectivenessReduce the time needed by the retrieval team to stabilise the child before transportImprove the child’s condition between time of initial call and time of retrieval team arrivalReduce diagnostic discordanceReduce the number of retrieved children being admitted to general wards at the tertiary hospitalReduce PICU LoS for retrieved childrenEconomic effectsFrom the health service perspective, be economically beneficial by reducing the number, and consequently the cost, of (i) retrievals, (ii) unnecessary tertiary hospital admissions, and (iii) LoS.

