#### Secondary outcome measures

Child’s physiological status using repeated measure scored using the Children’s Emergency Warning Tool (CEWT) (Authors: Royal Children’s Hospital, Queensland Health, unpublished) at two time points: (1) at time of initial call from the referring hospital (*CEWT*_*t*0_); and (2) at time of arrival of the retrieving team at the bedside at the referring hospital (*CEWT*_*t*2_).CEWT is an observation-chart based tool used within hospitals in Queensland. The tool is designed to identify patient deterioration and to trigger appropriate clinical escalations. The tool has nine components: respiratory rate, respiratory distress, Oxygen rate, Oxygen saturation, temperature, heart rate, blood pressure, capillary refill time, and level of consciousness. Observations are charted at the bedside, as with a conventional patient chart. Within each component, observations are translated to a score, on a scale of 1 (best) to 3 (worst). A score of ‘E’ and purple colour coding is used to prompt an emergency response (e.g. a respiratory rate <10 breaths/min, heart rate <60 beats/min or any component of blood pressure <50 mmHg).After each patient assessment, a total CEWT score is calculated by summing the component scores. A range of clinical responses are triggered by both significant negative changes in between-assessment component scores, and by the total CEWT score.Change in diagnosis (*DX*) using repeated measure taken at three time points: (1) at time of initial call to RSQ (*DX*_*t*0_); (2) at time of arrival of the retrieval team at the bedside at the referring hospital (*DX*_*t*2_); and (3) at time of arrival of the retrieval team and retrieved patient back at the PICU (*DX*_*t*5_).Destination of retrieved patients at the tertiary hospital (i.e. general ward vs. PICU).Retrieval decision (retrieval conducted/not conducted)PICU LoS for retrieved patients.

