**Table 2 Tab2:** **Statistical analyses for each outcome measure**

**Outcome measure**		**Statistical Method**
P1	Stabilisation time^1^	Linear regression with stabilisation time as the outcome, type of consultation as the main effect and PIM3 score as a co-variable
S1	Change in patient’s physiological status	Linear mixed effects model with physiological status as outcome, type of consultation and time as main effects, and a consultation-by-time interaction term.
S2	Change in diagnosis	Logistic mixed effects model with diagnosis as outcome, type of consultation and time as main effects, and a consultation-by-time interaction term.
S3	Destination of retrieved patients	Logistic regression with destination as outcome and type of consultation as the main effect.
S4	Retrieval decision	Logistic regression with retrieval decision as outcome and type of consultation as the main effect.
S5	PICU LoS^1^	Linear regression with LoS as the outcome, and type of consultation as the main effect.

^1^Data relating to stabilisation time and PICU LoS will transformed if necessary to meet assumptions of regression model.

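### Stabilisation time, destination and PICU length of stay exist only for retrieved children, but retrieval is decided after randomisation and telemedicine is expected to reduce it

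*Protocol article*

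**What the plan says.** The Randomisation and Patient recruitment sections place allocation at the initial retrieval call, before the consultation continues by video or telephone.

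Under Primary outcome measure, stabilisation time is t3 minus t2, the retrieval team's time at the referring hospital's bedside. On the population the section says: "We will analyse all participants after stratifying for initial risk". The Data analysis section applies intention to treat to the whole analysis.

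Under Secondary outcome measures, destination and PICU length of stay are restricted to retrieved patients, and one outcome is "Retrieval decision (retrieval conducted/not conducted". The Hypotheses section expects an economic benefit from "reducing the number, and consequently the cost, of (i) retrievals".

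Table 2 gives the models. P1 is a linear regression on consultation type with PIM3 as covariate. S3 is "Logistic regression with destination as outcome and type of consultation as the main effect". S5 is a linear regression on consultation type alone. Neither S3 nor S5 is adjusted for severity.

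The Sample size section expects 160 participants, 80 per arm, and claims "we have 80% power to detect a clinically important difference in stabilisation time" of 18 minutes. Its 20% attrition covers lack of consent and clinicians staying on the telephone. It does not cover children who are not retrieved.

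**The concern.** Three outcomes can be observed only in children who are retrieved, and retrieval comes after the randomised consultation. A comparison among retrieved children is protected by randomisation only if the consultation type does not change who is retrieved. The protocol expects that it does.

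If video lets the consultant keep milder children at the referring hospital, the retrieved children in the telemedicine arm are sicker on average than those in the telephone arm. Their stabilisation times and PICU stays would then tend to be longer even if telemedicine made no difference to any individual child. Success on the retrieval decision (S4) would partly mask a benefit on P1 and S5. PIM3 adjustment is planned for P1 only, and it removes only the part of the selection that PIM3 measures.

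S3 has a further mismatch. The hypothesis is about the number of retrieved children who go to general wards, while the model compares the share among those retrieved. When the number retrieved differs between arms, these are different questions.

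**Working it through.** **1. The plan's own figure.** Inputs from the Sample size section: SD 41 minutes, difference 18 minutes, 80 per arm, alpha 0.05 (taken as two-sided, because that reproduces the claim; one-sided gives 0.871).

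- Standard error = 41 × √(2/80) = 6.48 minutes.
- Power = Φ(18/6.48 − 1.96) = Φ(0.82) = 0.793.
- Detectable difference at 80% power = 6.48 × (1.96 + 0.84) = 18.2 minutes.

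The stated 80% is reproduced, but only when all 80 children in each arm have a stabilisation time, that is, when all are retrieved.

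**2. Power when some are not retrieved.** The article gives no retrieval share, so these shares are assumptions.

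| Retrieved, telephone / telemedicine | n per arm | Power for 18 min | Detectable difference |
|---|---|---|---|
| 100% / 100% | 80 / 80 | 0.793 | 18.2 min |
| 95% / 95% | 76 / 76 | 0.772 | 18.6 min |
| 90% / 90% | 72 / 72 | 0.750 | 19.1 min |
| 90% / 80% | 72 / 64 | 0.724 | 19.7 min |
| 80% / 70% | 64 / 56 | 0.670 | 21.0 min |

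For example, at 90% in each arm the standard error is 41 × √(2/72) = 6.83 and power is Φ(18/6.83 − 1.96) = 0.750.

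**3. Selection bias in P1.** Assume that telemedicine has no effect on any child's stabilisation time, that the mildest children are the ones not retrieved, and that the part of severity not captured by PIM3 has correlation ρ with stabilisation time. With share r retrieved, the mean among retrieved children rises by 41 × ρ × φ(z)/r, where z is the normal quantile at 1 − r.

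With ρ = 0.5 and every telephone-arm child retrieved:

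- 10% averted: 20.5 × 0.1755/0.90 = 4.0 minutes.
- 15% averted: 20.5 × 0.233/0.85 = 5.6 minutes.
- 20% averted: 20.5 × 0.280/0.80 = 7.2 minutes.

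All three shifts run against telemedicine. If 90% of the telephone arm is retrieved, the shift is the difference between arms: 7.2 − 4.0 = 3.2 minutes at 90% v 80%, and 6.2 minutes at 90% v 70%. Over ρ from 0.3 to 0.7 these become 1.9 to 4.4 and 3.7 to 8.7 minutes.

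**4. Effect on a true 18-minute benefit.** A shift of 4 to 7 minutes leaves an expected contrast of about 14 to 11 minutes. Allowing also for the smaller numbers, at ρ = 0.5 power falls to about 0.56 (90% v 80%) and 0.37 (90% v 70%).

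**5. Width of trimming bounds.** With 20% trimmed from a normal distribution with SD 41, each bound lies 41 × 0.280/0.80 = 14.3 minutes from the untrimmed estimate.

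**The case against.** - **The pool may be almost entirely retrieved children.** Only retrieval calls are randomised, advice-only calls are excluded, and the forecast of 200 calls in 24 months sits close to the 220 patients retrieved from the four sites over two earlier years. This stands as a limit on size: if nearly every call ends in retrieval in both arms, the bias is small. But then the hypothesis of fewer retrievals has little room, and the article gives no rate that would settle it.
- **A condensed article may leave undefined outcomes to the analysis plan.** That would answer a charge of missing detail. Here the article itself fixes the outcome, the population, the intention-to-treat principle and the models, and they do not fit together.
- **A team visit without transport might still yield a time.** Possibly; the figure that defines the time points is not shown. It does not help a child to whom no team is sent.
- **PIM3 adjustment reduces the bias.** Yes, for P1. The shifts above apply to the part of severity that PIM3 misses, and S3 and S5 have no adjustment.
- **S3 and S5 match their own definitions.** The destination outcome is defined among retrieved patients, and the length-of-stay hypothesis names retrieved children. A reader might infer that S3 is simply the wrong test. That is too strong: the model fits the outcome definition, and it is the hypothesis that is worded as a number. Nor need the share move against telemedicine. If the mildest children are kept back, the ward share among retrieved children would tend to fall.

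A reader might also infer that selection could reverse the primary result. This is not shown for the effect that the trial is designed to detect. Even if the averted 20% averaged a full SD below the mean, the shift would be 0.20 × 41/0.80 = 10.25 minutes, which attenuates an 18-minute benefit without reversing it.

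**Conclusion.** The point holds, and should be fixed. As written, analysis of all participants under intention to treat is impossible for stabilisation time, destination and PICU length of stay if any randomised child is not retrieved, and the comparisons that remain are conditional on an event that the intervention is meant to change.

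The size is uncertain. A shift of about 4 to 7 minutes against telemedicine rests on three assumptions: 10% to 20% of retrievals averted, the mildest children averted first, and a correlation of 0.5 between stabilisation time and severity that PIM3 does not capture. With near-universal retrieval it is small. The consequence for the primary outcome under this mechanism is a diluted benefit and lost power; a spurious benefit is not the risk. Separately, the 80% power is correct only if all 160 children are retrieved, and is about 0.75 if 90% are retrieved in each arm.

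**What to change.** 1. **P1.** Replace *all participants* with *all retrieved children* and label the comparison as conditional on retrieval. Report retrieval rates by arm beside it. Add a trimming-bounds sensitivity analysis, stating its monotonicity assumption (that telemedicine moves the retrieval decision in one direction only). State in the Sample size section that the 80% power assumes every participant is retrieved.
2. **S3.** Analyse all randomised children with the yes/no outcome of being retrieved and admitted to a general ward. This matches the hypothesis about the number of such children. Keep the share among retrieved children as a descriptive result.
3. **S5.** Beside the retrieved-only analysis, labelled as conditional, add an analysis of PICU days in all randomised children, counting 0 for those never admitted to the PICU. This answers a different question from the retrieved-only hypothesis, so it is added and does not replace it.

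Coding stabilisation time as zero for children who are not retrieved is not recommended, because it would count each avoided retrieval as faster stabilisation.

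The cost is a few lines of text and a little extra analysis. The retrieval decision is already an outcome, and the Data collection section already covers admission location at the tertiary hospital and length of stay by ward type. A child who is not retrieved is a *no* for S3 by definition. The main drawback is that the bounds may be wide, about 14 minutes either way at 20% trimming.
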